## Methods

This protocol was developed according to the Recommendations for Interventional Trials (SPIRIT) [36]. The trial was registered at the Chinese Clinical Trial Registry (www.chictr.org.cn) with the identifier ChiCTR2200057626 and approved by the local ethics committee (approval number: LDYYLL2022-55). Written informed consent was obtained from all enrolled patients.

### Objectives

This study aimed to investigate the potential of 30 mL of hemp seed oil in enhancing bowel cleansing. The study also evaluated the effect of reducing PEG by half by adding hemp seed oil and 5% sugar brine on reducing the adverse effects of bowel preparation and increasing the patients’ tolerance of PEG.

### Trial design and setting

This is a double-blind, single-center, three-arm, non-inferiority study that will be conducted at the Surgical Endoscopy Center of the First Hospital of Lanzhou University from April 2022 to February 2023. Recruited participants will be randomly assigned to receive a combination of 3 L of PEG, 30 mL of hemp seed oil and 2 L of PEG, or 30 mL of hemp seed oil, 2 L of PEG, and 1000 mL of 5% sugar brine (Fig. 1).

**Fig. 1 Fig1:**
[figure not shown]
Flow diagram of the patient’s enrolment. PEG, polyethylene glycol

### Participant selection

The following are the inclusion criteria: (1) age 50–70 years, (2) full cognitive capacity, (3) tolerance of intestinal preparation and colon examination, (4) patients undergoing colonoscopy, and (5) patients who agreed to participate, take research drugs as instructed, and sign informed content.

The following are the exclusion criteria: (1) participants who are allergic to any component of the experimental drug; (2) participants who cannot tolerate ordinary colonoscopy; (3) participants who have used research drugs, other intestinal preparations, or drugs that affect gastrointestinal motility within 7 days from the start of the trial; (4) participants who are diagnosed or suspected to have gastrointestinal obstruction, gastric retention, gastroparesis, disturbance of gastric emptying, or acute gastrointestinal bleeding; (5) participants with suspected abdominal organ perforation, including gastric perforation, intestinal perforation, and appendix perforation; (6) participants with a history of major gastrointestinal surgery; (7) women with positive pregnancy tests or pregnancy plans during the screening period; (8) participants with neurological diseases; (9) patients with severe heart disease or electrolyte imbalance that is difficult to correct; and (10) participants in other clinical trials within the last 3 months.

### Sample size

We calculated the expected sample size based on the preliminary extrapolation of the results of bowel preparation before the study began. According to the results of previous studies, when using 3 L PEG for bowel preparation, the qualified rate of bowel preparation was 80%. PEG was accepted as the standard preparation, and the aforementioned percentage was taken as a reference [18, 20, 37, 38]. Assuming the qualified rate of bowel preparation in this study is 85%, the alpha level was set to 0.05. When a sample size of 690 was calculated, a 5% difference between the three groups could be determined.

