### Recruitment, randomization, and blinding

Investigators trained for the study and authorized by the principal investigator will assess the candidates according to the inclusion and exclusion criteria on the day before the colonoscopy. After eligible participants are identified, written informed consent will be obtained from each eligible patient, next of kin, or legal representative. On the consent form, participants will be asked whether they agree to the use of their data and biological specimens. Participants will be asked to agree to the research team sharing relevant data with regulatory authorities as appropriate. Researchers should collect clinical data, including gender, age, weight, BMI, history of the previous colonoscopy, history of abdominal surgery, cardiovascular and neurological diseases, and long-term use of certain drugs.

Initially, the SPSS version 22.0 software will be used to generate random sequences, and these will be subsequently put in an opaque envelope. The independent statistical expert used a computer to generate random numbers, and the participants were assigned to the following 3 groups in a 1:1:1 ratio, numbered sequentially after random assignment: A, 3L PEG; B, 30 mL of hempseed oil and 2 L of PEG; and C, 30 mL of hemp seed oil, 2 L of PEG, and 5% sugar brine. Moreover, researchers, endoscopic physicians, and participants will all be blinded during the examination to eliminate bias as much as possible.

At the end of the study, unblinding will be carried out by the principal investigator. The first unblinding will be conducted to uncover the groups of participants, followed by statistical analysis to clarify the differences between the groups, and a second unblinding will be conducted to further clarify the specific groups. When an emergency, such as a serious adverse event, threatens the safety of a subject and the subject’s grouping must be known, an emergency unblinding would be conducted. The unblinding of the specific time, reason, and name of the executive of the emergency will be timely recorded.

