### Statistical analysis

In this study, we will adopt intent-to-treat and per-protocol methods to analyze all data. The basic information of patients is expressed by mean, median, and standard deviation. The chi-square test will be used to compare the categorical variables in the basic data of patients. In two independent samples, the Mann–Whitney *U*-test and Student’s test will be used for the comparison of continuous variables; the chi-square test will be used for the comparison of the main results; secondary outcomes will be compared using the chi-square test for categorical variables and Student’s *t*-test for continuous variables. All statistical analyses will be conducted with the 2-tailed test, and *P* < 0.05 will be considered statistically significant. We will make every attempt to collect complete information for all participants and avoid missing data. If necessary, missing data will be handled using multiple imputation. As no formal stopping rules have been specified for this study, no formal interim analyses are planned, and hence, no statistical testing will take place until the final analysis. All data were analyzed using SPSS 26 (SPSS Inc., an IBM Company, Chicago, IL).

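### The claim that 690 participants can determine a 5% difference does not fit the protocol's own inputs: with the planned two-sided chi-square test, power for 80% versus 85% is about 29%

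*Protocol article*

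**What the plan says.** The Sample size section of the protocol takes an adequate-preparation rate of 80% on 3 L PEG from earlier studies and continues: "Assuming the qualified rate of bowel preparation in this study is 85%, the alpha level was set to 0.05". It does not say which arm or arms the 85% belongs to. It concludes: "When a sample size of 690 was calculated, a 5% difference between the three groups could be determined".

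Three other places fix how that claim has to be read:

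- Recruitment, randomization, and blinding: "the participants were assigned to the following 3 groups in a 1:1:1 ratio", which makes 230 per arm.
- Statistical analysis: "the chi-square test will be used for the comparison of the main results", and "All statistical analyses will be conducted with the 2-tailed test", with significance at P < 0.05.
- Trial design and setting: the trial is described as a three-arm non-inferiority study. No margin is given there or elsewhere in the article.

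**The concern.** The sentence is a positive statement about what the trial can detect, and every input needed to test it except the power is given: two rates, alpha, total size, allocation and test. Detecting 80% versus 85% with conventional power usually takes many hundreds of participants per arm, so 230 looked far too few.

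The primary outcome is at stake. Suppose the difference test is carried out as planned and the assumed rates are true. A non-significant result would then be expected about 7 times in 10 (1 − 0.29 = 0.71). A reader who trusted the sample-size sentence would take that result as evidence against a 5-point difference, although the trial could not settle the question. The Discussion section expects the results to influence which regimens are prescribed.

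**Working it through.** **Inputs.** Control rate 0.80, study rate 0.85, alpha 0.05 and total 690 (Sample size); 1:1:1 allocation, so n = 690/3 = 230 per arm (Recruitment, randomization, and blinding); two-sided chi-square test (Statistical analysis). Two assumptions are mine: the 85% is read as the rate in the hemp seed oil arms, and 80% is used as the conventional power target because the article states none.

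**Can 690 be reproduced from these inputs?** For two proportions with pooled variance under the null:

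n = [1.96·√(2·p̄(1−p̄)) + 0.8416·√(p1(1−p1)+p2(1−p2))]² / d²

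With p̄ = 0.825 and d = 0.05: √(2 × 0.144375) = 0.5374 and √(0.16 + 0.1275) = 0.5362. So n = (1.0532 + 0.4513)² / 0.0025 = 905.4, or 906 per arm and 2,718 in total. For 90% power it is 1,212 per arm (3,636). The figure of 690 is not reproduced.

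**Power at 230 per arm.** Null standard error √(2 × 0.144375/230) = 0.03543; alternative standard error √(0.2875/230) = 0.03536.

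z = (0.05 − 1.96 × 0.03543)/0.03536 = −0.550, so power = Φ(−0.550) = 0.291. Simulation also gives 29.1%, or about 25% with the Yates correction.

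**Three-group chi-square, 2 df, rates 0.80/0.85/0.85.** Mean 0.8333; sum of squared deviations 0.001667; non-centrality 230 × 0.001667/0.13889 = 2.76; power 29.9%.

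**Other readings of a difference test**

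| Reading | Power for 80% vs 85% |
|---|---|
| One-sided 0.05, 230 per arm | 40.7% |
| Control vs both hemp seed oil arms pooled (230 vs 460), two-sided | 38.7% |
| 690 taken as per arm (the article gives 690 as the total) | 68.6% |

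None reaches 80%.

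**What 230 per arm can detect.** At 0.80 versus 0.894: p̄ = 0.847, null standard error 0.03357, alternative standard error 0.03328. Then z = (0.094 − 0.0658)/0.03328 = 0.85, giving power of about 80%. The detectable difference is about 9.4 points. The half-width of the 95% confidence interval at 80% and 85% is 1.96 × 0.03536 = 6.9 points, wider than the 5 points claimed.

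**Could 690 come from a non-inferiority calculation?** n = (zα + zβ)²·[p1(1−p1)+p2(1−p2)] / (margin + true advantage)². The margins, one-sided alphas and powers below are assumptions, because the article states none of them.

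| Assumed inputs | Per arm | Total |
|---|---|---|
| Margin 5 points, true 80% vs 85%, one-sided 0.025, power 80%: 7.849 × 0.2875/0.10² = 225.7 | 226 | 678 |
| Margin 10 points, true 85% vs 85%, one-sided 0.025, power 85%: (1.96+1.036)² × 0.255/0.10² = 228.9 | 229 | 687 |
| Margin 10 points, true 80% vs 80%, one-sided 0.05, power 85% | 231 | 693 |

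Under the 5-point margin, power at 230 per arm is Φ(0.10/0.03536 − 1.96) = Φ(0.868) = 80.7% if the new regimen is truly 5 points better. If both arms are at 80%, it is Φ(0.05/√(0.32/230) − 1.96) = Φ(−0.62) = 26.8%.

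**The case against.** The strongest reply is that this is a non-inferiority trial, so the 5% may be a badly worded margin. Power would then be about 81% at the assumed rates, and the expected 7-in-10 null result would not describe the primary conclusion. Part of this stands: the low power is a property of the difference test, not of every analysis the trial might run. But the documents do not establish the non-inferiority reading of the 5%. No margin is stated, the sentence speaks of determining a difference, and the planned two-tailed chi-square test does not test non-inferiority. Showing that a regimen is not more than 5 points worse is also different from detecting a 5-point difference.

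A reader might infer that 690 must come from a 5-point margin with an assumed 5-point advantage. The arithmetic does not support that: a 10-point margin with equal rates fits at least as closely (687 or 693, against 678). The matches do not identify the method.

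A second reply is that an article condenses the full protocol, so power, margin and dropout may be stated there. That is fair, and their absence is not the point. The point rests on a claim that is made and that the article's own figures contradict.

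**Conclusion.** The statement is wrong as written. For 80% versus 85% at 230 per arm, the planned two-sided 0.05 chi-square test has about 29% power between two arms and about 30% across three arms (80/85/85). About 906 per arm would be needed for 80% power; the trial as sized reaches 80% power only at about 80% versus 89.4%.

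This rests on the stated rates, alpha, allocation and test, on reading the 85% as the rate in the hemp seed oil arms, and on 80% as the conventional power target. The 29% itself does not depend on that target.

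Two stronger conclusions might be drawn, and the documents support neither. One is that the trial is underpowered for whatever it sets out to show: under some non-inferiority inputs 230 per arm is adequate, but the article does not show which inputs, if any, were used. The other is that the sample must be enlarged: the error is in the stated property, and restating it correctly removes the error.

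**What to change.** Keep 690 and delete the sentence that a 5% difference could be determined. Then make the sample-size basis and the Statistical analysis section agree, in one of two ways.

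- **If the aim is a difference test:** state that 230 per arm gives about 29% power for 80% versus 85% with the two-sided 0.05 chi-square test, and 80% power only for a difference of about 9.4 points.
- **If the aim is non-inferiority:** state the margin, one-sided alpha, assumed true rates and resulting power, including the power if the arms are equal. For a 5-point margin, for example, that is 81% if the new regimen is truly 5 points better and 27% if both arms are at 80%. Replace the chi-square test as the primary analysis with a confidence interval for the difference in adequate-preparation rates, compared with that margin. The margin should be the one used in the original calculation if it can be recovered; in any case it should be fixed before unblinding.

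The cost is a rewritten sample-size paragraph, a changed primary-analysis sentence under the second option, and the submission to the Ethics Committee and registry update that the Protocol amendments section already provides for. No extra participants are needed. The drawback is that the published figure becomes less favourable.

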### Recruitment, randomization, and blinding

Investigators trained for the study and authorized by the principal investigator will assess the candidates according to the inclusion and exclusion criteria on the day before the colonoscopy. After eligible participants are identified, written informed consent will be obtained from each eligible patient, next of kin, or legal representative. On the consent form, participants will be asked whether they agree to the use of their data and biological specimens. Participants will be asked to agree to the research team sharing relevant data with regulatory authorities as appropriate. Researchers should collect clinical data, including gender, age, weight, BMI, history of the previous colonoscopy, history of abdominal surgery, cardiovascular and neurological diseases, and long-term use of certain drugs.

Initially, the SPSS version 22.0 software will be used to generate random sequences, and these will be subsequently put in an opaque envelope. The independent statistical expert used a computer to generate random numbers, and the participants were assigned to the following 3 groups in a 1:1:1 ratio, numbered sequentially after random assignment: A, 3L PEG; B, 30 mL of hempseed oil and 2 L of PEG; and C, 30 mL of hemp seed oil, 2 L of PEG, and 5% sugar brine. Moreover, researchers, endoscopic physicians, and participants will all be blinded during the examination to eliminate bias as much as possible.

At the end of the study, unblinding will be carried out by the principal investigator. The first unblinding will be conducted to uncover the groups of participants, followed by statistical analysis to clarify the differences between the groups, and a second unblinding will be conducted to further clarify the specific groups. When an emergency, such as a serious adverse event, threatens the safety of a subject and the subject’s grouping must be known, an emergency unblinding would be conducted. The unblinding of the specific time, reason, and name of the executive of the emergency will be timely recorded.

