## Introduction

Colorectal cancer is a common malignant tumor of the digestive system. According to a report of the cancer survey, colorectal cancer ranks in the top three in new cases and deaths in both men and women, making it one of the most life-threatening cancers among Chinese patients [1, 2]. The progression of colorectal adenomas to cancer may take up to 10 years, and the incidence increases with age [3–6]. Moreover, the risk of mortality from colorectal cancer has been reported to decrease by 53% in patients who underwent endoscopic adenoma resection [7–10]. Many factors affect the quality of colonoscopy, of which bowel preparation is an essential factor. Inadequate bowel preparation can reduce the adenoma detection rate, prolong the duration of colonoscopy, and increase the risk of examination [11–13].

Currently, polyethylene glycol (PEG) is still the first choice for clinical intestinal preparation. Due to its poor taste, the need to drink a lot of water and adverse events, such as nausea and vomiting, patients have reduced tolerance and medical compliance for PEG [14, 15]. According to a survey, the incidence of constipation is higher among middle-aged and elderly patients than among younger patients owing to factors such as a decline in intestinal function and dietary habits, affecting the quality of bowel preparation [16, 17]. Recently, many clinical studies on bowel preparation are being conducted with the aim of improving the quality of bowel preparation and patients’ tolerance. Examples of such studies include those on the application of ascorbic acid, senna, and sodium phosphatases [18–21]. However, many trials have not achieved the expected results pertaining to bowel preparation. Therefore, improving the quality of bowel preparation and reducing the amount of PEG is still a problem that needs to be solved.

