### Study endpoints

#### Primary outcomes

The effect of intestinal preparation was regarded as the main outcome indicator and was scored using the Boston Bowel Preparation Scale (BBPS). As a commonly used clinical bowel preparation assessment scale, the BBPS score divides the large intestine into 3 segments (rectum and sigmoid colon, transverse colon and descending colon, ascending colon and cecum) and scores after adequate bowel preparation. Each intestinal segment was scored from 0 to 3 points, and the total score ranges from 0 to 9 points. The indications of scorings were as follows: 0 points, the entire intestinal mucosa cannot be observed due to irremovable solid or liquid feces; 1 point, parts of the intestinal mucosa cannot be observed due to the presence of stains, turbid liquid, and residual feces; 2 points, the intestinal mucosa is well observed, but a small amount of stains, cloudy liquid, and feces remain; and 3 points, the intestinal mucosa is well observed, and there are no residual stains, cloudy liquids, and stools [39]. In this study, the total score of BBPS score is > 5, and any intestinal segment ≥ 2 points can be considered satisfactory intestinal preparation.

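### The primary chi-square test is valid, but it gives no effect estimate or interval and leaves baseline data already collected unused, so some precision may be lost

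*Protocol article*

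**What the plan says.** - **Design.** Under Trial design and setting, the protocol article describes a "double-blind, single-center, three-arm, non-inferiority study". It states no margin.
- **Endpoint.** Under Primary outcomes, the Boston scale is reduced to a yes/no result: "the total score of BBPS score is > 5, and any intestinal segment ≥ 2 points can be considered satisfactory intestinal preparation".
- **Baseline data.** Under Recruitment, randomization, and blinding, researchers are to record "clinical data, including gender, age, weight, BMI, history of the previous colonoscopy, history of abdominal surgery", plus cardiovascular and neurological disease and long-term drug use. Allocation is 1:1:1 and no stratification factor is named.
- **Analysis.** Under Statistical analysis, "the chi-square test will be used for the comparison of the main results". Tests are two-sided at 0.05. No covariate, risk difference or confidence interval is mentioned.
- **Use of the baseline data.** Apart from descriptive summaries, the stated use is comparison between groups: "The chi-square test will be used to compare the categorical variables in the basic data of patients".
- **Sample size.** The reference is that "when using 3 L PEG for bowel preparation, the qualified rate of bowel preparation was 80" per cent. The article continues "Assuming the qualified rate of bowel preparation in this study is 85" per cent, with alpha 0.05 and a total of 690. Power, margin and dropout are not given.

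**The concern.** Two features of the planned primary analysis could be improved at almost no cost.

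First, a chi-square test returns a P value for equality. A trial described as non-inferiority is read from an interval for the difference between each new regimen and 3 L PEG, and the stated test does not produce one.

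Second, variables that may predict bowel cleanliness are recorded before treatment and then left out of the main comparison. If they do predict the outcome, adjusting for them narrows the interval and removes the effect of chance imbalance in them. The randomisation as described is unstratified, so neither design nor analysis does anything further about such imbalance.

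The gain depends on how prognostic these variables are. The Introduction offers one lead: it reports that "the incidence of constipation is higher among middle-aged and elderly patients" than among younger ones, and says this affects preparation quality.

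**Working it through.** **Inputs from the article.** Total 690, so 690/3 = 230 per arm; rates 80% and 85%; two-sided alpha 0.05. **Assumed, because the article does not give them:** R² (the share of outcome variance explained by the covariates), a margin of 5 points where a non-inferiority calculation is shown, and 80% power where a sample size is computed.

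**1. The plan's own figure.** 690 cannot be reproduced from the stated inputs, because power and margin are missing.
- Read as detecting 80% vs 85% with a two-sided test at 80% power: n = [1.96·√(2·0.825·0.175) + 0.8416·√(0.16 + 0.1275)]² / 0.05² ≈ 906 per arm, 2718 in total. With 230 per arm the power is 29.1%.
- Read as non-inferiority with a 5-point margin, true rates 80% (control) and 85% (new), one-sided 0.025 and 80% power: n = (1.96 + 0.8416)²·0.2875 / 0.10² ≈ 226 per arm, 678 in total. This is close to 690, but so are other assumption sets. For example, 85% in both arms, a 10-point margin, one-sided 0.05, 90% power and 5% dropout gives 693.

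**2. Unadjusted precision.** SE = √[(0.80·0.20 + 0.85·0.15)/230] = √(0.2875/230) = 0.0354. The 95% half-width is 1.96·0.0354 ≈ 6.9 percentage points.

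**3. Effect of adjustment.** To a good approximation the variance is multiplied by (1 − R²), so 230 per arm acts like 230/(1 − R²).

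| Assumed R² | Effective total N | SE | Superiority power, 80 vs 85 | Non-inferiority power, assumed 5-point margin, 80 vs 85 | Same margin, 80 vs 80 |
|---|---|---|---|---|---|
| 0 | 690 | 0.0354 | 29.1% | 80.7% | 26.8% |
| 0.01 | 697 | 0.0352 | 29.4% | 81.1% | 27.0% |
| 0.02 | 704 | 0.0350 | 29.6% | 81.5% | 27.2% |
| 0.05 | 726 | 0.0345 | 30.4% | 82.7% | 27.9% |
| 0.10 | 767 | 0.0335 | 31.8% | 84.6% | 29.2% |

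At R² = 0.10 the half-width is 1.96·0.0335 ≈ 6.6 points instead of 6.9.

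**4. Check by simulation.** Logistic standardisation was compared with the raw difference (230 per arm, 80% vs 85%, one prognostic score, 4000 runs per setting).

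| Odds ratio per SD of the score | R² | Variance, adjusted / unadjusted |
|---|---|---|
| 1.00 | 0 | 1.005 |
| 1.28 | 0.010 | 0.994 |
| 1.49 | 0.025 | 0.980 |
| 1.82 | 0.054 | 0.938 |
| 2.23 | 0.092 | 0.923 |

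So the change runs from about +0.5% to about −8% of variance in simulation, and to −10% by the formula at R² = 0.10. The simulation fitted a single score. A list of six uninformative terms would cost somewhat more, roughly 6/460 ≈ 1.3% of variance for a two-arm contrast, which is still small.

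**5. What the article says about prognosis.** The factor it ties to preparation quality is constipation, which is not among the baseline items named. Age is recorded, but entry is limited to 50–70 years, so much of the older-versus-younger contrast is gone. Neurological disease and major gastrointestinal surgery are exclusions; other abdominal surgery can still vary. For sex, BMI and prior colonoscopy the article claims no link with the Boston score.

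**The case against.** The case against making this a point is substantial, and much of it stands.

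- **The planned test is valid.** With unstratified randomisation the unadjusted comparison is unbiased, and no stratification factor has been left out of the model. A reader might infer that the analysis is wrong or biased; the article does not support that.
- **Prognostic value is not shown.** A reader might infer that known prognostic information is being discarded. The article never calls the recorded variables prognostic, and its entry criteria narrow several of them. R² near zero is possible, and then nothing is gained.
- **Adjustment does not rescue power.** The 29.1% figure is for a superiority test and reaches only 31.8% at R² = 0.10. Nor is there yet a defined non-inferiority contrast to sharpen, because no margin is stated and the chi-square tests equality.
- **No data-driven covariate choice is planned.** A reader might infer one from the baseline significance tests. The article plans no adjusted model, so barring such selection is a safeguard that goes with the proposed change and does not correct anything stated.
- **Adjusted analyses often sit in a statistical analysis plan, which is not shown.** This holds for supportive analyses. The primary test, however, is fixed in the article itself, so the choice can be commented on.

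What remains is that the stated method yields no estimate or interval, and that a better one is available from data already in hand with very little to lose.

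**Conclusion.** The point holds as a minor recommendation. The unadjusted chi-square is a valid test, but it is a poor vehicle for a non-inferiority question and may forgo some precision. The size rests wholly on an assumed R². Over 0 to 0.10 it runs from no gain to a variance reduction of about 8–10%, or up to about 77 participants' worth of information (767 − 690). Under the assumed 5-point margin with 80% vs 85%, that is at most about 4 points of power (80.7% to 84.6%). The missing margin and the unsupported sample size are separate, matter more, and should be settled first; this change repairs neither.

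**What to change.** In Statistical analysis, replace the chi-square for the primary endpoint with the following.

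- A logistic model of satisfactory preparation on arm plus age, sex, BMI, prior abdominal surgery and prior colonoscopy. Add baseline constipation if it is on the case report form.
- Marginal standardisation of that model to give adjusted risk differences with 95% CIs for B−A and C−A.
- The unadjusted risk difference with 95% CI as a sensitivity analysis.
- A statement that the covariate list is fixed before the first unblinding and that no covariate is added or dropped on the strength of the baseline tests.

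Once a margin has been stated and justified, these intervals can be compared with it.

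The cost is a short passage of text, a few lines of code, and the amendment and registry update that the article already provides for. The software sentence names only SPSS 26 and should allow another package if the standardised difference is computed elsewhere. No new data or participants are needed. If the covariates prove uninformative, the price is a variance increase of around 1% or less.
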